### Phase 5: data analysis and synthesis of study findings (October 2018–October 2019)

#### Quantitative methods

Quantitative data will be analysed using Stata V.15 and reported using descriptive statistics. Within the context of this realist evaluation, we were keen to use the quantitative data to address a single hypothesis, namely whether nominal possession of an EPaCCS record was associated with increased chance of dying at home. However, logistic regression will be used to determine the adjusted OR and 95% CI for the associations between having an EPaCCS record and dying at home, considering other factors of interest, including, but not limited to: age, sex, deprivation and underlying cause of death.

Of approximately 8000 deaths occurring in the CCG area over the year of study, we expect around 10% (800 deaths) of patients to have an EPaCCS.^10^ If the proportion of deaths occurring at home is expected to be 25% among those without an EPaCCS, we would have over 99% power to detect an absolute increase of 10% to 35% among those with an EPaCCS. The power would be about 84% if the proportion were increased by 5% to 30%.

Descriptive statistics will be employed to report EPaCCS usage.

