**Figure 2 F2:**
[figure not shown]
Visual representation of the initial programme theory at a macro level. ACP, advanced care planning; EPaCCS. electronic palliative care coordination systems.

**Table 1 T1:** Programme theory for the EPaCCs study, comprising the 17 CMO statements that inform the programme theory, and the questions that will be used, in the focus group with the end-of-life board, to investigate each CMO statement

EPaCCs process	CMOs	Focus group questions
**Commissioning**	1. If the strategy behind the EPaCCs is definable, deliverable and measureable, the aim, purpose and outcomes of EPaCCS will be clear. ***(strategy)***	How will you evaluate EPaCCS success? What are the markers of success for you? What is the CCGs long term vision for the EPaCCS?
	2. If HCPs engage with the EPaCCS positively on early usage and see it as an improvement on any previous EOL register, HCPs will engage positively with EPaCCS. ***(engagement)***	Given that the previous EOL register was generally not well thought of, or used, how did the CCG plan to get HCPs on board? How do you think the EPaCCS has been received?
**Commissioning/uptake/adoption**	3. If the EPaCCS is well-publicised and marketed to all stakeholders HCPs will be aware of EPaCCS, understand the aim and purpose of the EPaCCS, and will initiate an EPaCCs template and/or access an EPaCCS record. ***(publicity)***	How was the EPaCCS publicised and marketed to different groups of HCPs? What are your views on how effective this has been? How aware do you think HCPs are of EPaCCS and do you think they understand its purpose and importance?
	4. If HCPs receive sufficient support and training, so that they know how to use it, they and will initiate an EPaCCs template and/or access an EPaCCS record. ***(training)***	Can you tell us about the CCG strategy for providing training and support to different groups of HCPs in the EPaCCS roll-out? What do you think about this, and how effective it has been?
**Uptake/adoption**	5. If HCPs have the time and/or resources to learn a new system, an EPaCCS template will be initiated. ***(time and resources)***	There are a significant number of GP practices that have not initiated an EPaCCS – do you have any thoughts about why this might be? Do you think all HCPs will have the time and resources (ie, they are connected to a computer, have internet and NHS network access) to learn and new system and access EPaCCS?

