### Phase 3: individual interviews with HCPs, patients, current and bereaved carers (November 2018–July 2019)

#### Healthcare professionals

HCPs from community nursing teams, primary care, the ambulance service, the local hospices, care homes and secondary care will be invited to participate.

GPs working in practices within the CCG area will be invited to support the study and the study team will purposively sample from a list of practices, to include practices that are high-users of EPaCCS and low users of EPaCCS based on data compiled by the CCG.

The research team will purposively sample HCPs who express an interest in participating according to gender, age and profession to ensure maximum variation in the sample. All interviews with HCPs will take place over the telephone for both pragmatic and methodological reasons. Conducting interviews over the telephone will reduce the time and cost to the study that may be involved in travelling to interviews and well-planned telephone interviews can gather the same material as those held face to face.^28^

A topic guide, informed by the evolving programme theory, will be used to ensure consistency across the interviews. This will enable the research team to compare the views of each group at the stage of data analysis. Interviews will last approximately 30 min and it is anticipated that approximately 3–5 HCPs will be interviewed from each group (18–30 in total).

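### The home-death regression names no GP practice term and its 84% power assumes independent deaths, although the article shows that EPaCCS use varies by practice

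*Protocol article*

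**What the plan says.** Under Phase 5, Quantitative methods, the protocol article plans that "logistic regression will be used to determine the adjusted OR and 95% CI". The outcome is death at home and the exposure is possession of a record. The adjustment is described in these terms: "considering other factors of interest, including, but not limited to: age, sex, deprivation and underlying cause of death". The list is open, but every named factor is a patient characteristic. Practice is not mentioned, nor is clustering, a random effect or a robust variance.

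The power calculation starts from the number of deaths: "Of approximately 8000 deaths occurring in the CCG area over the year of study, we expect around 10% (800 deaths) of patients". The reference rate is then given: "If the proportion of deaths occurring at home is expected to be 25% among those without an EPaCCS". For the larger effect the article claims "over 99% power to detect an absolute increase of 10% to 35% among those with an EPaCCS". For the smaller effect, with the rate in per cent, it says: "The power would be about 84% if the proportion were increased by 5% to 30".

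Elsewhere the article describes uptake as uneven between practices. A focus-group question in Table 1 (statement 5) says: "There are a significant number of GP practices that have not initiated an EPaCCS". In Phase 3, practices are sampled "to include practices that are high-users of EPaCCS and low users of EPaCCS", and the section on patients and carers defines high use as more than 20 records, the median over practices, four months after implementation. In Phase 4, the number of records created by each surgery is collected, for description of usage.

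**The concern.** A record is usually opened by the patient's GP or community nurse, and several Table 1 statements tie uptake to training, time, incentives and access, some of which act on a whole practice. Exposure is therefore likely to cluster by practice. If home death also clusters, for example through local community nursing, hospice or care-home supply, two things follow for a model without practice.

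- **Precision.** Ordinary logistic standard errors would be too small, so the 95% CI would cover less than 95% and the test would reject too often.
- **Confounding.** If practices that took up EPaCCS early already had more home deaths, the odds ratio would partly compare practices. The Background asks whether EPaCCS changes practice or only records what already happens, and calls earlier comparisons potentially biased and confounded. A model without practice is poorly placed to answer that.

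The power statement has the same gap: it leaves no room for clustering or for covariate adjustment.

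**Working it through.** **1. Reproduce the stated power.** Inputs from Quantitative methods: 800 deaths with a record, 7200 without, 25% against 30%. Two-sided 5% is inferred from the 95% CI.

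- Unpooled SE = √(0.25×0.75/7200 + 0.30×0.70/800) = 0.01699. Power = Φ(0.05/0.01699 − 1.96) = Φ(0.98) = 83.7%.
- Pooled null SE, with overall proportion 0.255: √(0.255×0.745×(1/7200 + 1/800)) = 0.01624. Power = Φ((0.05 − 1.96×0.01624)/0.01699) = Φ(1.07) = 85.8%.
- For 25% against 35%, both versions exceed 99.9%.

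The stated 84% is thus correct arithmetic for independent deaths without adjustment.

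**2. Assumptions for clustering.** The article gives neither the number of practices nor any ICC. Assumed main range: 50–100 practices (m = 8000/practices = 160 to 80 deaths each), exposure ICC ρx = 0.1–0.3, home-death ICC ρy = 0.01–0.02. Low case: ρx = 0.05, ρy = 0.005.

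**3. Unclustered test.** Exposure varies within practices, so the variance inflation is DE = 1 + (m − 1)ρxρy, and the type I error of a test that ignores it is 2{1 − Φ(1.96/√DE)}.

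- Low case, 100 practices: DE = 1 + 79×0.05×0.005 = 1.02; type I error 5.2%.
- Mild end: 1 + 79×0.1×0.01 = 1.08; 5.9%.
- Middle, 80 practices, ρx 0.2, ρy 0.02: 1 + 99×0.004 = 1.40; 9.7%; CI should be √1.40 = 1.18 times as wide.
- Upper end, 50 practices, ρx 0.3, ρy 0.02: 1 + 159×0.006 = 1.95; 16.1%; CI 1.40 times as wide.

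Simulation of clustered deaths agrees. In the middle case the unclustered SE averaged 0.016 against a true SD of about 0.020, with type I error of about 9–11%.

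**4. Power of a practice-stratified analysis.** Stratifying removes between-practice variation but uses only within-practice exposure contrast, a fraction of about 1 − ρx of the information. From the pooled formula, power ≈ Φ((0.05√(1 − ρx) − 1.96×0.01624)/0.01699).

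- ρx = 0.1: Φ((0.0474 − 0.0318)/0.0170) = Φ(0.92) = 82%.
- ρx = 0.3: Φ((0.0418 − 0.0318)/0.0170) = Φ(0.59) = 72%.

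The comparable independent-deaths figure is the pooled 85.8%. Simulation with a practice-stratified test gave about 71–83% over the main range and about 82–84% in the low case. In the middle case it gave about 79%, against about 73% for an unstratified comparison with cluster-robust SEs.

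**5. The 10-point scenario.** The null SE is √(0.26×0.74×(1/7200 + 1/800)) = 0.01635 and the alternative SE 0.01762. Stratified at ρx = 0.3: Φ((0.0837 − 0.0320)/0.0176) = Φ(2.93) = 99.8%. Unstratified at DE 1.95: Φ((0.0715 − 0.0320)/0.0176) = Φ(2.24) = 98.8%.

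**6. Confounding.** With 80 practices, ρx 0.2, ρy 0.02 and an assumed correlation of 0.3 between practice uptake and practice home-death rate, the simulated unstratified difference under no effect was about 2.3–2.4 points, nearly half of the 5 points being powered. Stratifying by practice removed it; cluster-robust SEs alone did not.

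**The case against.** The article is condensed, its covariate list is explicitly open, and variance estimation is often left to a full plan. It nowhere says that practice will be left out. The evidence of clustering is also limited. The high/low split is an interview-sampling device, a median cut always yields two groups, and raw record counts mix practice size with uptake. The remark about practices without records belongs to a focus group planned for October 2018, while the cohort runs to 21 February 2019. Nothing in the article documents variation in home death by practice, and adjustment for deprivation, age and cause of death may absorb part of it. The cohort is all adult deaths in a year, so the power figure sets no recruitment target.

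Most of this stands as a limit on the claim. A reader might infer that the interval is too narrow, or that confounding remains, as settled facts. The article does not support that: both depend on practice being absent from the final model and on home death varying by practice. Nor is the 84% a miscalculation. The cluster-trial inflation 1 + (m − 1)ρy would also exaggerate the loss, because patients with and without a record can share a practice.

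What survives is that the article does commit to a model type, named covariates and a power figure, that the figure has no allowance for clustering, and that the article's own account of uptake makes practice the obvious omitted factor.

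**Conclusion.** The point holds in conditional form. The stated 84% is an independent-deaths, unadjusted figure, and the named model has only patient-level covariates although EPaCCS use varies by practice. If practice is not modelled and home death varies by practice, the CI is too narrow and the odds ratio mixes within-practice and between-practice differences.

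The size is not derivable from the article. It ranges from negligible (type I error about 5%, power about 82–84%) in the low case to a type I error of about 6–16% over the main range. The 2.3–2.4 point bias rests on one further assumption, the 0.3 correlation. The issue bears on the 5-point scenario; the 10-point conclusion is essentially unchanged. This is a worthwhile, inexpensive improvement and does not invalidate the study.

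**What to change.** - Extract a practice identifier for each death with the EMIS Web data. The article does not say that it is held per patient; this is likely, given the data source and the per-surgery counts, but should be confirmed.
- Add practice to the logistic regression, either as fixed effects or as a random intercept together with the practice's EPaCCS rate, with practice-clustered standard errors. Clustered standard errors alone would not deal with confounding by practice.
- State that the 84% for the 5-point difference assumes independent deaths and no covariate adjustment, or give power over a stated range of ICCs for the model actually used (about 71–83% for a practice-stratified analysis under the main assumptions above).

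Cost: one extra data field, a model option in Stata and one sentence. The CI will be somewhat wider, and with fixed effects the practices with no EPaCCS deaths contribute nothing to the contrast.

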#### Qualitative methods

Data analysis will be conducted using a realist approach informed by Jackson and Kolla’s realistic evaluation analysis method.^29^ This analytic process will involve the following steps:

Coding individual units (a discrete C, M or O) within the narratives of the interviews.Identifying the complex connections that link these codes together into dyads or triads.Subsuming the linked codes into themes using thematic analysis.^30^

Analysis will begin shortly after data collection starts and be ongoing and iterative. Analysis will inform further data collection: for instance, analytic insights from data gathered in earlier interviews will be used to develop and adapt the programme theory and in turn, identify any changes that need to be made to the topic guide for use during later interviews. The study will generate new programme theories to explain how the EPaCCS works, for whom and any contextual influences and constraining factors that affect their initiation and usage. Emerging analysis and findings will be discussed with PPI representatives, to explore and clarify findings.

Qualitative and quantitative data will be collected concurrently, giving equal weight to each.^30^ Data will be triangulated in order to test and refine the programme theories, accepting that any findings are fallible and with time and further study new data are bound to emerge.^31^ The synthesised study findings will establish the potential outcomes of EPaCCS, identify the underlying mechanisms which explain how they produce these effects and highlight the key contextual factors that affect their success or failure. Recommendations can then be made for the development and implementation of EPaCCS.

### Patient and public involvement

To support the development of this study protocol, members of the study team (LF and LP) presented and discussed an outline proposal of this study to patients, staff and carers at the local hospice on two separate occasions in April 2018. Approximately 10 participants voluntarily took part in these, semi-structured, discussions, in which we asked specific questions concerning ethical and methodological issues. Participants were also encouraged to ask any questions. These meetings raised several important issues which have been incorporated into the design of this study. Such issues included allowing patients the choice of whether to have a carer sit alongside them during their interview and which HCPs they felt it was important that the study team spoke to, due to the involvement they had in providing care for patients. The meetings also discussed what terms, wording and questions would be acceptable to patients and carers to read and hear in the study information documents and interviews.

At the end of both meetings, patients and carers were invited to continue to support the design of the study should they wished. Two members came forward expressing a wish to be more actively involved in the study. They have kindly been involved in reviewing all the study literature, including the topic guides, study information sheets and the lay summary for this protocol. It is hoped that they will wish to continue their involvement with the study. This will include informing the content of materials for lay audiences, drawing links to groups and forums that the research team may be unaware of, and supporting the study team with the interpretation and dissemination of study findings. To ensure ongoing PPI, all patients and carers taking part in the study will be invited to support the ongoing development of the study.

### Ethics and dissemination

The study has been approved by NHS South West–Frenchay Research Ethics Committee (REC reference number: 18/SW/0198). The research team will disseminate the findings to a range of stakeholders. We will draw on the networks and expertise of the local CCG EOL care board to disseminate the research outputs widely and appropriately. Key audiences include patient and carer organisations, GPs and community nursing teams in primary care, ambulatory services and care home staff, HCPs working in secondary palliative care services and hospices, managers and directors within healthcare organisations with responsibility to provide high-quality services within budget and healthcare policy-makers, nationally and internationally.
